**3. Art und Zahl der Prüfstellen**

1 Center (monocenter study)

**4. Has an application of similar content been filed before with another ethics committee?**

No.

## **5. Written consent of the director of the respective clinic**

has been filed (Appendix 1)

## **6. and 7. Documentation of study-related additional costs, financing plan, third money**

The trial will be sponsored by MSD Sharp & Dohme GmbH, München. For accounting of the study an account has been established with the administration of the University clinic Cologne (account no. 3620/1394/31 (letter of the administrative director of 10 December 2003)

## **8. Consulting fee**

Written agreement that in case of an industry-sponsored study the consulting fee will be booked directly from an account of the administration of the University clinic Cologne ([name]) (Appendix 2).

## **10. Multicenter trials**

This trial is a monocenter study.  
Approximately 60 subjects will be recruited at the University of Cologne.

## **B. Description of the trial**

### **1. Scientific goals**

see Appendix 3

### **2. Study protocol**

see Appendix 4

### **3. Planned invasive measures and burden expected for the participants**

The subjects will take oral study medication through the treatment period of 2 weeks (1 or 2 tablets daily). Furthermore, blood will be drawn three times, twice at baseline and once at the end of the study.

### **4. Patient selection**

see Appendix 5

### **5. Kind of study (in drug studies: phase?)**

- |                           |     |
|---------------------------|-----|
| a) diagnostic study?      | no  |
| b) therapeutic study      | no  |
| c) tolerability study?    | no  |
| d) epidemiological study? | no  |
| e) other study?           | yes |

This is a pharmacodynamic pilot study with 2 approved drugs (phase 4) which should extend current knowledge about effects and mechanisms of action. The study is an investigator-initiated trial.

### **6. Which laws and regulations apply?**

- |                              |     |
|------------------------------|-----|
| a) Arzneimittelgesetz?       | yes |
| b) Strahlenschutzgesetz?     | no  |
| c) Röntgenverordnung?        | no  |
| d) Medizingeräte-Verordnung? | no  |
| e) Grundsätze                | yes |
| f) Meldung RP                | yes |

## **7. Which prestudies have been done?**

Two approved drugs will be investigated which are widely marketed. There were no specific prestudies.

Pharmacologic-toxicologic studies:

a) performed?

Yes, drug approval files are available at the Federal Institute for Drugs and Medical Devices (BfArM). There is an abundance of medical scientific literature on ezetimibe and simvastatin.

b) Results filed with the German drug agency?

Yes, within the framework of drug approval (Ezetrol®, Zocor®)

c) Summary of relevant results for the performance of this study  
see general scientific literature on ezetimibe/simvastatin

## **8. Possible complications and/or risks?**

Two approved and marketed lipid-lowering drugs will be used, whose safety and tolerability has been documented in the international literature and in the approval files. For further information see Fachinformationen ([Appendix 6](#)).

## **9. Risk-benefit-considerations**

This is a study in healthy subjects which is intended to increase biochemical insights. The subjects will have no direct benefit from participating in the trial but the burden of short-term medication will be justifiable in view of the expected scientific results.

## **10. Interim analysis and criteria for early termination**

There will be no interim analysis. The planned number of participants and the analyses will have to be reached before the study will be evaluated.

The termination criteria for the individual participant will be according to general clinical practice using ezetimibe or simvastatin.

Early termination of the whole trial will not be expected, therefore no specific criteria will be defined for this event. The decision about an early termination will be made by the principle investigator.

## **11. and 12. Informed consent**

see [Appendix 7](#)

## **13. Professional secrecy**

see [Appendix 7](#)

## **14. Insurance?**

see Appendix 8

### **15. Financial plan?**

Financing the study is guaranteed (see A.6 and A.7).

### C. Kurzfassung (German)

Ezetimib senkt das Gesamtcholesterin und das LDL-Cholesterin über eine Hemmung der intestinalen Cholesterinresorption, wodurch es zu einem kompensatorischen Anstieg der endogenen Cholesterinsynthese kommt. Die genauen zugrunde liegenden regulatorischen Mechanismen des durch Ezetimib induzierten Anstiegs der Cholesterinsynthese und der Abnahme des LDL-Cholesterin sind nicht bekannt. Darüber hinaus wurde nie untersucht, ob Veränderungen der Expression des LDL-Rezeptors zum Cholesterin senkenden Effekt von Ezetimib beitragen.

Die vorliegende Studie untersucht, ob Änderungen in der LDL-Rezeptor-Expression und in den Konzentrationen der HMG-CoA-Reduktase-mRNA unter Behandlung mit Ezetimib zu beobachten sind. Zum Vergleich werden die Wirkungen einer Behandlung mit Simvastatin und die kombinierte Gabe von Simvastatin und Ezetimib untersucht. Da das Profil der mRNA-Expressionen Informationen über die Wirkungen auf der Transkriptionsebene, aber nicht notwendigerweise auch auf der translationalen Ebene gibt, werden auch Veränderungen des LDL-Rezeptor-Proteins auf der Zelloberfläche von mononukleären Zellen untersucht. Als ein funktioneller Marker der HMG-CoA-Reduktase-Aktivität wird die Ratio der Konzentration von Lathosterin zu Cholesterin im Serum verwendet, da diese mit der Aktivität der HMG-CoA-Reduktase korreliert und auch als Marker der Gesamtcholesterinsynthese herangezogen werden kann.

In diesem Zusammenhang konnte gezeigt werden, dass pflanzliche Sterole, die auch über eine Hemmung der intestinalen Cholesterinresorption wirken, die Synthese von Gesamtcholesterin und LDL-Cholesterin steigern, die Konzentrationen der LDL-Rezeptor-mRNA steigern und auch die Konzentrationen des LDL-Rezeptor-Proteins steigern, aber keinen signifikanten Effekt auf die Expression der HMG-CoA-Reduktase oder Aktivität in peripheren mononukleären Blutzellen haben.

Das Ziel dieser prospektiven randomisierten Parallelgruppenstudie ist es zu untersuchen, ob die Behandlung mit Ezetimib Veränderungen in der HMG-CoA-Reduktase-Aktivität/-Expression oder in der LDL-Rezeptor-Expression/-Protein-Konzentration in mononukleären Blutzellen hat. Zu diesem Zweck werden drei Parallelgruppen mit je 20 erwachsenen Männern (gesund, ohne Medikation, weitgehend normalgewichtig) gebildet. Eine Gruppe wird mit Ezetimib 10 mg/Tag, die andere mit Simvastatin 40 mg/Tag und die dritte mit Ezetimib plus Simvastatin in den genannten Dosierungen behandelt. Die Behandlungsdauer beträgt 2 Wochen. Vor Beginn der Behandlung sowie am Ende der Behandlung werden jeweils Blutproben entnommen, die bei -80 °C eingefroren werden. Die in dieser Studie bestimmten Parameter sind die Lipoproteinkonzentrationen, die Isolation von mononukleären Zellen, die Messung der LDL-Rezeptor-mRNA in peripheren mononukleären Zellen, die Messung der HMG-CoA-Reduktase-mRNA in peripheren mononukleären Zellen und die Bestimmung der LDL-Rezeptor-Protein-Konzentrationen auf der Oberfläche von peripheren mononukleären Zellen im Blut. Darüber hinaus werden die Konzentrationen von Lathosterin und Cholesterin im Serum bestimmt, deren Ratio als Surrogatmarker für die HMG-CoA-Reduktase-Aktivität verwendet wird.

Zur Teilnahme an der Studie kommen männliche Probanden in Frage, die mental und linguistisch in der Lage sind, die Ziele der Studie zu verstehen und eine genügende Compliance besitzen, das Studienprotokoll einzuhalten, sich im Alter zwischen 18 und 60 Jahren befinden, in einem allgemein guten Gesundheitszustand befinden (festgestellt aufgrund der Anamnese, der körperlichen Untersuchung und der Laboruntersuchung), einen Body mass index zwischen 18,5 und 30 kg/m^2 haben, ein LDL-Cholesterin < 190 mg/dl und Triglyzeride < 250 mg/dl haben, einen normalen Blutdruck (< 140/90 mmHg haben (eine isolierte systolische Hypertonie (RR syst. > 140 mmHg, diast. < 90 mmHg ist akzeptable, falls ansonsten ein ausreichender Gesundheitszustand besteht), und insbesondere keines der folgenden Ausschlusskriterien aufweisen: aktive Lebererkrankung oder ungeklärte und andauernde Erhöhung der Serum-Transaminasen, Cholestase, Myopathie.

## Summary

Ezetimibe decreases serum total and LDL cholesterol levels by blocking cholesterol absorption in the intestine, causing a compensatory increase in cholesterol synthesis. The exact underlying regulatory mechanisms of the ezetimibe-induced increase in cholesterol synthesis and decrease in serum LDL cholesterol are not known. In addition, it has never been investigated whether changes in LDL receptor expression contribute to the LDL-lowering effect of ezetimibe, as is the case with other agents causing a decrease in cholesterol absorption such as the plant stanols.

In the present study, we plan to examine changes in LDL receptor and HMG-CoA reductase mRNA concentrations during ezetimibe treatment. For comparison, effects of simvastatin and the combined administration of the two will be investigated. Since mRNA expression profiles provide information about effects at the transcriptional but not necessarily at the translational level, we will also analyze changes in the LDL receptor protein at the cell surface of mononuclear blood cells. As a functional marker for HMG-CoA reductase activity the ratio of serum lathosterol to cholesterol concentration will be used since it correlates with HMG-CoA reductase activity and serves also as a marker of total cholesterol synthesis.

In this regard it has been shown that plant sterols, which also act by blocking intestinal cholesterol absorption, increase cholesterol synthesis, decrease LDL synthesis, increase LDL receptor mRNA levels as well as LDL receptor protein concentrations but have no significant effect on HMG-CoA reductase expression or activity in peripheral blood mononuclear cells. Aim of this prospective randomized parallel study is to examine changes in HMG-CoA reductase activity/expression and in LDL receptor expression/protein concentration in mononuclear blood cells under treatment with ezetimibe.

For this purpose 3 parallel groups of 20 healthy men will be formed. One group will be treated with ezetimibe (10 mg/day), one with 40 mg/day of simvastatin and another with ezetimibe (10 mg/day) plus simvastatin (40 mg/day). Each treatment period will last for 2 weeks. Blood drawing will be performed at baseline (before the initiation of treatment) and at the end of the 2 weeks. (storing of the samples at  $-80^{\circ}$ ). The measurements involved in this study include the determination of the lipoprotein concentrations in serum, isolation of the mononuclear cells, measurement of LDL receptor mRNA from the peripheral blood mononuclear cells, measurement of HMG-CoA reductase mRNA levels in peripheral blood mononuclear cells, measurement of the LDL-receptor protein concentrations on the surface of peripheral blood mononuclear cells. Furthermore, the serum lathosterol to cholesterol concentrations will be measured as a surrogate marker of the HMG-CoA reductase activity.

### **Appendix 3:**

#### **Scientific Background**

Cells in the human body need cholesterol which can be derived from endogenous synthesis or from receptor-mediated uptake of circulating lipoproteins such as intermediate density lipoproteins (IDL) and low density lipoproteins (LDL) (1). Circulating lipoproteins are taken up by various receptors, all with their own specific ligands. LDL, for example, is mainly endocytosed by a specific apoB/E receptor, known as the LDL receptor. Transcription of the LDL receptor gene is up-regulated by low cellular free sterol concentrations and is initiated by activated sterol response element binding proteins (SREBPs) (2). The transcription of the rate-limiting enzyme for endogenous cholesterol synthesis, 3-hydroxy-methyl-glutaryl coenzyme A (HMG-CoA) reductase, is controlled in a similar way (3), although its activity depends on post-transcriptional modifications (4).

The benefits of lipid-lowering therapy on coronary heart disease (CHD) risk have been clearly established in many large-scale primary and secondary prevention trials. Although statins (HMG-CoA reductase inhibitors) have been shown to be effective in lowering LDL cholesterol, many patients do not achieve the standard treatment goals. Although higher doses of statins are more effective in lipid lowering, the risk of serious side effects seems to be dose dependent (5). Therefore the need of additional lipid-lowering compounds, not acting as HMG-CoA reductase inhibitors, has focused attention on drugs with different mechanisms of action such as the inhibition of intestinal cholesterol absorption (6). Intestinal cholesterol absorption shows great inter-individual variation and ranges from 20–80 % (7–9). It is known that a decrease in cholesterol absorption caused by consumption of foods enriched in plant sterols is associated with an increase in cholesterol synthesis (10).

Ezetimibe is a compound of the 2-azetidinone class that has been shown to produce a marked inhibition of intestinal cholesterol absorption of 54 % in humans, a compensatory increase of cholesterol synthesis and a decrease in LDL- and total cholesterol (11). In animal models the ezetimibe-induced inhibition of cholesterol absorption ranges between 92–96 % in a dose range of 1–10 mg/kg (12;13). A dose of 10 mg daily has been shown to decrease LDL cholesterol in the range of 17–20 % (14). It does not affect the absorption of triglycerides or fat-soluble vitamins (11). Studies in bile duct cannulated rats show that intraduodenally delivered ezetimibe undergoes rapid and extensive metabolism to its phenolic glucuronide in the intestine. In the portal vein, more than 95 % of ezetimibe is already glucuronidated and ezetimibe acts directly in the intestine as a glucuronide (15).

The aforementioned observed ezetimibe-induced increase in cholesterol synthesis might explain the favorable effects of co-administration of ezetimibe and statins (16). In this context, in vivo experiments in humans assessing the effect of ezetimibe on the activity of drug-metabolizing enzymes revealed no effect on the activity of the cytochrome P450 (CYP) isoenzymes CYP1A2, CYP2C8/9, CYP2D6, CYP3A4 or N-acetyltransferase (17). Thus, the pharmacokinetic interaction potency of ezetimibe seems to be low. Co-administration of ezetimibe with statins produces an incremental 12–15 % decrease in LDL cholesterol, independent of kind and dose of the co-administered statin (11). When ezetimibe is added to an ongoing statin therapy, LDL cholesterol is incrementally reduced by 21.5 % (relative to on-statin baseline values) compared with placebo (6;11). Thus, because statins can reduce the compensatory increase in the hepatic cholesterol synthesis induced by ezetimibe, the combination of ezetimibe and statins results in an incremental lowering of LDL cholesterol concentrations. The observed benefit in lipid lowering efficacy in the combined therapy is presumably predominantly caused by synergistic pharmacodynamic interactions, since the pharmacokinetics of neither statins nor ezetimibe seem to be altered in clinically relevant ways when these agents are used in combination (18). Adding 10 mg ezetimibe to a low-dose statin therapy is as effective as approximately tripling the statin dose in monotherapy, assuming an additional lipid lowering effect of 5–6 % when doubling the dose of statins (19).

Ezetimibe acts at the brush border of the small intestine and inhibits the uptake of dietary and biliary cholesterol into the enterocytes (15). It does not act via adenosine triphosphate-binding cassette (ABC)

transporters such as ABCA1, ABCG5 or ABCG8, which regulate cholesterol efflux in enterocytes (20) or via the scavenger receptor class B, type I (SR-BI), a receptor expressed in the liver and enterocytes, which is suggested to play a role in cholesterol absorption (21). Indeed, little is known about the molecular target of ezetimibe. Recently, an integral membrane protein of approximately 145 kDa could be identified in the rabbit small intestine brush border membrane as one potential component of the postulated intestinal cholesterol transporter (22). In comparison to other compounds, intestinal cholesterol absorption by ezetimibe is more pronounced than that observed for other known inhibitors of cholesterol absorption including neomycin and plant sterol and -stanol esters in humans (11). Neomycin has been shown to reduce cholesterol absorption in a dose-dependent manner by 26–49 % (23–25). Treatment with high-dose plant sterols and stanols have shown to lower cholesterol absorption by up to 45 %, but the maximal effects are observed under circumstances in which the active agents are delivered in fat carriers in conjunction with cholesterol meals (26).

The exact underlying regulatory mechanisms of the ezetimibe-induced increase in cholesterol synthesis are not known. In this context, it has been shown that plant sterols, other substances that block intestinal cholesterol absorption, increase cholesterol synthesis (27–29), decrease LDL synthesis (30), increase LDL receptor mRNA levels and LDL receptor protein concentrations but have no effect on the HMG-CoA reductase expression in peripheral mononuclear cells (29).

Mononuclear cells are a heterogeneous cell population, and, when cultured in lipoprotein-deficient serum, bind and degrade more [ $^{125}$ I]LDL than lymphocytes do (31). Furthermore, monocytes incorporate ~20-fold more [2- $^{14}$ C]mevalonate into sterols than lymphocytes do (32). These findings suggest that cholesterol metabolism is more active in monocytes than in lymphocytes. Moreover, a positive relationship exists for LDL receptor and HMG-CoA reductase mRNA expression in mononuclear blood cells and the liver (33).

### **Purpose of the study**

Purpose of the present study is to elucidate the mechanisms involved in the ezetimibe-induced increase in cholesterol synthesis and to examine whether changes in the LDL receptor expression contribute to its LDL-lowering effects. In specific, in the present study we will examine changes in the LDL receptor and HMG-CoA reductase mRNA concentrations under ezetimibe treatment alone (10 mg/day), under a treatment with a statin (simvastatin 40 mg/day) and under a combination treatment of ezetimibe plus simvastatin. Furthermore, since the mRNA expression provides information about effects at the transcriptional but not necessarily at the translational level, we will also analyze changes in the LDL receptor protein at the cell surface of mononuclear blood cells as well as the HMG-CoA reductase activity. As a marker of total cholesterol synthesis, the ratio of lathosterol to cholesterol in serum will be used (34), since this ratio correlates with the hepatic HMG-CoA reductase activity (35). It has been recently shown that an increased HMG-CoA reductase activity does not correlate with HMG-CoA reductase mRNA concentrations (29). This may suggest that HMG-CoA reductase activity is not only regulated at a transcriptional level, but that post-transcriptional steps are also important. In this context it has also been shown that in rats cholesterol feeding lowers HMG-CoA reductase expression at the level of translation and not at a transcriptional level (36;37). Others, however, have reported in rats a clear correlation between HMG-CoA reductase mRNA and cholesterol synthesis after cholesterol feeding (38). These contradictory findings illustrate that the mechanisms regulating HMG-CoA activity are complex and need further study.

## **Appendix 4:**

### **Study protocol**

#### **Study medication**

- Group A: ezetimibe 10 mg/day
- Group B: simvastatin 40 mg/day
- Group C: ezetimibe 10 mg/day plus simvastatin 40 mg/day

Study medication will be obtained free of charge through the hospital pharmacy of the University of Cologne (“Handelsware Ezetrol® 10 mg, Zocor® forte”).

There will be open label treatment.

#### **Objectives**

##### *Primary objective*

To determine the effects of ezetimibe and simvastatin on the HMG-CoA reductase activity and expression as well as on the LDL receptor expression and -protein concentration in mononuclear blood cells of healthy men.

#### **Description of the clinical trial**

##### **Study design**

A prospective, randomized, parallel 3-group study

##### **Randomization**

Eligibility for study participation will be determined by use of a standardized medical history questionnaire. Informed consent will be obtained, a physical examination and screening routine laboratory chemistry will be performed. All enrolled patients will be randomized to receive either ezetimibe, simvastatin or both.

Randomization will be performed according to a predetermined random list (balanced 6-block design) by use of sealed envelopes.

Before randomization, all selection criteria must be checked by filling in the inclusion/exclusion criteria form in the CRF.

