### **Number of centers and number of subjects**

*Number of investigational sites:* This is a one-center trial.

*Number of subjects:* A total number of subjects of 20 in each treatment group is required (20 completed cases per group, drop-outs will be replaced). Total number: 60 completed subjects.

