#### *Exclusion criteria*

- Intake of lipid lowering drugs within 12 weeks of study entry
- Excessive alcohol intake
- Disease of the liver (known active liver disease, e.g. chronic virus hepatitis, cholestatic liver disease, any unexplained or ongoing elevation of serum liver transaminases > 2 x ULN)
- Disease of the gastrointestinal tract (e.g. chronic inflammatory bowel disease)
- Renal dysfunction (glomerular filtration rate < 60 ml/min as calculated by the formula of Cockcroft & Gault)
- Coronary heart disease
- Eating disorders (anorexia or bulimia nervosa)
- History of recent substantial weight change, history of obesity > II° (BMI > 35 kg/m^2)
- Diabetes or other endocrine disorders
- Use of medication known to affect serum lipoprotein metabolism
- Any other disease/disorder or condition which might in the investigator's opinion preclude the subject from participation in the study

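### The protocol discloses a single block size of 6 in an open-label, one-centre trial, so staff who keep count could foresee about one allocation in five

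*Protocol*

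**What the plan says.** The Randomization section of Appendix 4 prescribes a "predetermined random list (balanced 6-block design) by use of sealed envelopes". The Study design section describes "A prospective, randomized, parallel 3-group study", and the Study medication section says "There will be open label treatment". On sites, the section on numbers of centres and subjects says "This is a one-center trial". The same section sets the target at 20 completers in each of three groups, 60 in all, with drop-outs replaced.

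Two further passages bear on how men enter. The Randomization section requires: "Before randomization, all selection criteria must be checked by filling in the inclusion/exclusion criteria form in the CRF". The entry criteria in Appendix 5 are mostly numeric or diagnostic. However, one inclusion criterion leaves general health to the investigator's judgement, and the last exclusion criterion reads "Any other disease/disorder or condition which might in the investigator's opinion preclude the subject from participation in the study".

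The protocol gives no second block size and no stratification. It does not say who holds or opens the envelopes, or how a replacement is allocated.

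**The concern.** Sealed envelopes protect the next allocation only if it cannot be worked out from the earlier ones. With a single known block size, anyone who sees the earlier allocations can count down the block, and the last man's arm is then always known. Open treatment at one site makes the earlier allocations easy to see, and the protocol itself prints the number needed for the count.

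What is at stake is comparability of the three groups at entry. Someone who knows which arm comes next could bring a volunteer forward, hold him back or judge him unsuitable. The judgement-based entry criteria leave some room for this. With 20 men per arm, a few steered entries could shift a group's baseline.

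**Working it through.** **Inputs.** Block size 6 (Appendix 4, Randomization); three arms (Study design); 20 completers per arm, 60 in total (Number of centers and number of subjects). Assumption for the worst case: the observer knows the block size, the block boundaries and every earlier allocation.

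**The plan's own figure.** 60 / 6 = 10 blocks; 6 / 3 = 2 men per arm per block; 10 × 2 = 20 per arm. This matches the stated target.

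**Predictability within one block.** A block has 6!/(2!·2!·2!) = 90 equally likely orders. The remaining places start at (2, 2, 2).

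- *Next allocation certain.* This needs all remaining places to belong to one arm. At position 5 the last two places must be the same arm, with probability 1/5. At position 6 it always holds.
- *At least one arm ruled out.* Position 3: the first two are the same arm, 1/5. Position 4: one minus the probability that the first three all differ, 1 − (4/5 × 2/4) = 3/5. Positions 5 and 6: always.
- *Best guess correct.* This is the largest remaining count divided by the places left, averaged over histories. For example, at position 4 the remainder is (1, 1, 1) with probability 2/5 and (0, 1, 2) with probability 3/5, so 2/5 × 1/3 + 3/5 × 2/3 = 8/15.

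| Position | 1 | 2 | 3 | 4 | 5 | 6 | Sum per block |
|---|---|---|---|---|---|---|---|
| Certain | 0 | 0 | 0 | 0 | 1/5 | 1 | 1.2 |
| An arm ruled out | 0 | 0 | 1/5 | 3/5 | 1 | 1 | 2.8 |
| Best guess correct | 1/3 | 2/5 | 1/2 | 8/15 | 3/5 | 1 | 3.37 |

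**Over ten blocks (60 men).**

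- Certain: 12 expected, or 20%. Each block contributes one or two, so the number lies between 10 and 20.
- An arm ruled out: 28 expected, or 46.7%. This includes the certain ones.
- Best guess correct: 33.7 expected, or 56.1%, against 60 / 3 = 20 (33.3%) by chance.

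**Effect of varying the block size.** The sizes 6, 9 and 12 are an illustrative assumption, not the plan's. In a simulation of 1,000 lists of 60, the observer knew which sizes were possible but not the size of each block.

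| Per 60 allocations | Blocks of 6 | Random 6, 9 or 12 |
|---|---|---|
| Certain | 12.0 | about 1.4 |
| An arm ruled out | 28.0 | about 4.2 |
| Best guess correct | 33.7 | about 31.5 |

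The guessing advantage over chance falls only from 33.7 − 20 = 13.7 to 31.5 − 20 = 11.5, so about 11.5 / 13.7 = 84% of it remains.

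**The case against.** The strongest reply is that the protocol nowhere says that the enrolling person sees the earlier allocations or keeps a tally. It is silent on who holds and opens the envelopes, and a separate procedure may settle this. That stands: the figures are upper bounds for a perfect tracker, and even for him 80% of allocations stay uncertain. Having an arm ruled out is also not the same as knowing the allocation.

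The motive is weak too. The subjects are healthy men who expect no direct benefit (section B.9), every arm receives active drug, and the study parameters are laboratory measures taken before and at the end of treatment. The eligibility form must be completed before randomization, which limits exclusion after an envelope is opened. All of this lowers the likely bias. It does not stop someone foreseeing the next arm by counting before the form is filled in.

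A reader might infer two stronger things. One is that allocation concealment is defeated. The documents do not support this: they show an opportunity, not that anyone has the knowledge or would use it. The other is that the wording means six blocks of 10 men, which could not be balanced over three arms. The protocol calls the design balanced, and ten blocks of 6 give exactly the 20 per arm it requires, so a block size of 6 is the tenable reading.

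**Conclusion.** The point holds as a cheap improvement to the design; nothing in the protocol is miscalculated or contradictory here. Following the stated rule for 60 men leaves at least 10 allocations, and 12 on average, known in advance to anyone who counts. This rests on three assumptions: one block size throughout, enrolling staff who know it, and earlier allocations visible to them without delay. If custody of the envelopes already keeps that information from those who enrol, the exposure is smaller.

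Replacements could add to it. If a replacement simply took the drop-out's arm, his allocation would be known outright, but the protocol does not say that this is the rule.

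**What to change.** Before the first subject:

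1. Replace the list with one built from randomly ordered block sizes (for example 6, 9 and 12), and extend it beyond 60 entries so that replacements are drawn from it.
2. Remove the block size from the protocol, and keep the sizes from enrolling staff.
3. Have someone who does not enrol prepare the list and hold the envelopes. Each is opened only after the eligibility form is complete and enrolment is recorded.

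The third step is needed because varied blocks remove most of the certainty but little of the guessing advantage. One permuted list of exactly 60 would lower best guesses further, to about 25.5 of 60, but would leave no entries for the replacements that the protocol promises.

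The cost is one regenerated list, an edit to the Randomization section and a named custodian role. The downside is a small possible imbalance between arms: stopping inside a block of 12 can leave two arms up to 4 men apart, against 2 within a block of 6.
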